Whether the presence of a high-risk delivery variable (forceps, prolonged second stage of labour, shoulder dystocia, anal sphincter laceration) modifies the association between MVPA in the early postpartum period on pelvic floor support and symptoms at 1 year (exploratory aim).	(a) The prevalence risk of worse pelvic floor support at 1 year will be higher for women with greater MVPA in the early postpartum period, higher in women with a high-risk delivery variable; and even higher for women with both.(b) The prevalence risk of greater pelvic floor symptoms at 1 year will be higher for women with greater MVPA in the early postpartum period, higher in women with a high-risk delivery variable; and even higher for women with both.	0.05	1.70
Whether each of grip strength and abdominal muscle endurance is associated with pelvic floor support and symptoms, independent of PFM, all measured at 1 year.	(a) Greater grip strength and greater abdominal muscle endurance are each associated with better pelvic floor support, adjusted for PFM strength.(b) Greater grip strength and greater abdominal muscle endurance are each associated with fewer symptoms, adjusted for PFM strength.*	0.025	1.78
Whether abdominal muscle endurance measured at 8 weeks predicts pelvic floor support and symptoms at 1 year.	(a) Greater abdominal muscle endurance at 8 weeks predicts better pelvic floor support 1 year postpartum.(b) Greater abdominal muscle endurance at 8 weeks predicts fewer symptoms 1 year postpartum.	0.05	1.70
The components of habitus, measured at 1 year that are associated with poor pelvic floor support and symptoms at 1 year.	(a) At 1 year postpartum, greater adiposity, as per cent body fat, and body mass index are associated with worse pelvic floor support.(b) At 1 year postpartum, greater adiposity, as per cent body fat, and body mass index are associated with greater symptoms.	0.05	1.70
Whether waist circumference at 8 weeks postpartum predicts pelvic floor support and symptoms at 1 year.	(a) Greater waist circumference at 8 weeks postpartum predicts worse pelvic floor support 1 year postpartum(b) Greater waist circumference at 8 weeks postpartum predicts greater pelvic floor symptoms 1 year postpartum.	0.05	1.70

*We use an adjusted two-sided significance level of 0.05/2=0.025, reflecting two hypothesis tests from two independent.

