†We use an adjusted two-sided significance level of 0.017 to accommodate three separate binomial regression models for statistical interaction terms between each test of muscular fitness and IAP.

IAP, intra-abdominal pressure; MVPA, moderate-to-vigorous physical activity; PFM, pelvic floor muscle strength.

We base our sample size estimate on the proportion of women expected to demonstrate pelvic floor support at or below the hymen (ie, MVD≥0 cm indicating worse support). (Based on pilot data, a higher proportion of women are expected to meet the criteria for symptom burden, our second primary outcome.) Of 10 studies identified at the onset of this research that use the POP-Q to assess vaginal support during the first postpartum year, 7 measured support 6–12 months postpartum^20^
^27^
^29^
^87–90^ (total n=1215); and 4 at 6 weeks to 6 months postpartum^21^
^22^
^28^
^91^ (total n=671). The mean anterior vaginal wall support was always worse (more positive) than the mean posterior vaginal wall or mean apical support. The distribution of stage in studies providing this ranged from 0% to 30%, 26% to 65%, 28% to 59%, and from 0% to 5% for stages I, II and III, respectively.^20–22^ The proportion of women with MVD≥0 ranged from 0% to 41%.^20^
^22^
^28^
^87^
^88^
^90^ In a pilot study of Utah women, similar to our expected population (unpublished), 18% had MVD≥0 at 1 year postpartum. We elected to conservatively estimate the proportion of women with MVD≥0 as 15%.

Sample size determinations were performed using PASS 2008. Consistent with Dunnett and Goldsmith,^92^ we did not adjust for multiplicity based on our two primary outcomes, as the inference related to the study aim does not require the simultaneous examination of the two comparisons.

Our predictors are continuous variables. We consider women at the mean for a given predictor as ‘low risk’ and those at the mean plus 1SD as ‘high risk’. Assuming that the frequency of MVD≥0 is 15% in the low-risk group and R^2^ of the predictor regressed on other predictors is 0.5, a sample size of 585 women at 1 year follow-up provides 90% power to detect the minimal OR shown in table 2 for women whose predictor value is 1SD higher than other women whose value is at the mean. (R^2^ is likely to be lower; if so, this sample size provides 90% power to detect even lower odds).

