#### Quantitative data

The study population will consist of primiparous women who delivered vaginally and were followed longitudinally for 1 year. We will perform descriptive statistics, stratified by ethnicity, to characterise the population and will characterise the trajectories of key variables by plotting longitudinal patterns at the third trimester, and at 8 weeks and 1 year postpartum.

In this cohort study, we cannot remove prevalent cases as it is not feasible to measure pelvic floor support in this large population before pregnancy, though cases of MVD≥0 are rare in nulliparas.^97^ Since we cannot estimate true risk ratios, we will calculate the prevalence ratio for each outcome at 1 year postpartum based on each predictor, as well as model prevalence ratios using modified generalised linear models, such as logistic regression with variance correction by GEE.^98^

Analyses of dichotomous outcomes will begin with a univariate analysis of prevalence ratios and CIs for the primary predictor and potential confounders. Further modelling by multivariable modified logistic regression will adjust potential confounders based on a directed acyclic graph.^99^
^100^ We will avoid adjusting for variables downstream of a predictor in the causal path.^99^ Effect modification will be considered when cell sizes permit. Models will be checked for adequacy of the model, multicollinearity, influential observations, etc, using standard regression diagnostics. We do not anticipate time-dependent confounders since each hypothesis addresses a specific time relative to delivery. In the final analysis, missing values will be imputed as needed using sequential regression multiple imputation (ICE in Stata or IVEWARE with SAS).^101^

Nominal p values and 95% CIs will be reported. All tests will be two-sided, at the conventional 5% significance level, except as noted. When there are multiple tests to be performed simultaneously, for example, several scenarios or several predictors to be tested in separate models, we will use a proper multiple test correction to adjust for the inflation of type I error. Analysis will be performed in SAS, Stata or R.

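### Within-aim multiplicity is written as fixed Bonferroni levels (0.025, 0.017); naming Holm's step-down would keep the same family-wise control and gain some power at almost no cost

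*Protocol article*

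**What the plan says.** Table 2 (Study aims and adequacy of sample size for quantitative projects) gives each aim a two-sided level and a minimal detectable odds ratio (OR). Most aims have 0.05 and 1.70. Three aims have a reduced level:

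- Intra-abdominal pressure (IAP) at 8 weeks, in two tasks: 0.025, OR 1.78.
- Grip strength and abdominal muscle endurance at 1 year: 0.025, OR 1.78.
- Three fitness measures as modifiers of IAP during lifting: 0.017, OR 1.82.

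The footnote for the two-test aims reads "We use an adjusted two-sided significance level of 0.05/2=0.025, reflecting two hypothesis tests". The footnote for the interaction aim reads "We use an adjusted two-sided significance level of 0.017 to accommodate three separate binomial regression models for statistical interaction terms".

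The Quantitative data section states "All tests will be two-sided, at the conventional 5% significance level, except as noted". For several tests done together it adds "we will use a proper multiple test correction to adjust for the inflation of type I error", with no method named. On reporting it says "Nominal p values and 95% CIs will be reported". Across outcomes, "we did not adjust for multiplicity based on our two primary outcomes".

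**The concern.** The footnotes use the present tense of a rule, and the analysis section makes an exception for levels noted elsewhere. Read together, each hypothesis in these three aims is judged against its own fixed level, whatever the other p values in the family show. That is single-step Bonferroni.

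The cost falls on the second and third rejections. Suppose IAP during lifting gives p=0.001 and IAP during endurance testing gives p=0.03. At a fixed 0.025 the second is not significant. Under Holm, once the first is rejected, the second is tested at 0.05 and is significant, with family-wise error still held at 0.05. These aims ask about each member of the family (both tasks, each of two fitness measures, each of three modifiers), so later rejections are part of the answer sought.

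A common reason to prefer Bonferroni is that it comes with simple matching simultaneous confidence intervals. The plan reports nominal p values and 95% intervals, so a move to Holm loses none.

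**Working it through.** **Inputs.** From the sample size section: N=585 at 1 year and 90% power ("a sample size of 585 women at 1 year follow-up provides 90% power to detect the minimal OR shown in table 2"); event proportion 0.15 and R² 0.5 ("Assuming that the frequency of MVD≥0 is 15% in the low-risk group and R^2^ of the predictor regressed on other predictors is 0.5"); effect expressed as an OR per 1 SD of a continuous predictor. From Table 2: levels 0.05, 0.025 and 0.017. The correlation between test statistics within a family is not given; 0 to 0.6 is assumed.

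**Step 1: reproduce Table 2.** For logistic regression with a continuous covariate,

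OR = exp[(z₁₋α/₂ + z₀.₉₀) / √(N·p·(1−p)·(1−R²))].

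The denominator is √(585 × 0.15 × 0.85 × 0.5) = √37.29 = 6.107, and z₀.₉₀ = 1.282.

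- α=0.05: exp[(1.960+1.282)/6.107] = 1.700 (stated 1.70)
- α=0.025: exp[(2.241+1.282)/6.107] = 1.780 (stated 1.78)
- α=0.017: exp[(2.387+1.282)/6.107] = 1.823 (stated 1.82)

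Table 2 is reproduced.

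**Step 2: identify the procedure.** 2 × 0.025 = 0.05, and 0.05/3 = 0.01667, which the plan rounds up to 0.017. Both are plain Bonferroni. The rounded level sums to 3 × 0.017 = 0.051, and under independence its family-wise error is 1 − (1 − 0.017)³ = 0.0501, a negligible excess.

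**Step 3: define Holm.** Order the p values. Test the smallest at 0.05/m, the next at 0.05/(m−1), and so on, stopping at the first non-rejection. The first step equals Bonferroni at 0.05/m, so Holm rejects whatever Bonferroni at exactly 0.05/m rejects, and sometimes more.

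**Step 4: compare power.** One million draws of correlated normal test statistics were simulated per setting. Non-centrality was 6.107 × ln(1.78) = 3.521 for two tests and 6.107 × ln(1.82) = 3.657 for three. Bonferroni was run at 0.025 and at exactly 0.05/3. The Table 2 OR for the interactions is taken at face value. Ranges are over correlations 0 to 0.6.

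| Family | Effects real | Measure | Bonferroni | Holm |
|---|---|---|---|---|
| 2 tests, OR 1.78 | both | per test | 90% | 93-94% |
| | both | both detected | 81-84% | 88-90% |
| | one | that one | 90% | 90% |
| 3 tests, OR 1.82 | all three | per test | 90% | 94-95% |
| | all three | all detected | 72-79% | 87-89% |
| | two | both detected | 80-83% | 85-87% |
| | one | that one | 90% | 90% |

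With one real effect the gain is about 0.1 to 0.2 percentage points. Power to detect at least one effect is essentially the same (three independent tests, all real: 99.9% under both). Simulated family-wise error under Holm did not exceed 0.05 in any setting.

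**Step 5: compare with the level as printed.** Against 0.017 rather than 0.05/3, Holm is not strictly dominant. A smallest p value of 0.0168 passes 0.017 but fails Holm's first step of 0.01667. The effect on power is trivial: at OR 1.82, power is 89.8% at 0.017 and 89.7% at 0.05/3.

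**The case against.** The strongest reply is that nothing here is wrong. Bonferroni is valid and conventional, and it lets each model be judged without reference to the others. That stands: this is an improvement, not a correction.

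Second, the levels sit in a table of sample size considerations, where first-step levels are the right planning inputs under Holm too, and the unnamed correction in the analysis section leaves room for Holm. This stands in part. The footnotes and the exception clause make fixed levels the natural reading, but a reader who concludes that the plan rules out a step-down procedure goes further than the text does.

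Third, the larger gains need every effect in the family to be real at the planning OR. For the interaction aim that means three separate interactions, each at 1.82. The 90% starting point may also be low, since the article expects R² below 0.5 and a higher frequency for the symptom outcome. With an assumed R² of 0.25 and the other inputs unchanged, per-test power at OR 1.78 and level 0.025 is already about 98%, and Holm adds about 1 point. This stands, and it limits the size of the point.

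Fourth, nominal p values will be published, so a reader could apply Holm unaided. That is true, but the study's own declared conclusions would still follow the fixed levels.

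A reader might also infer that Holm lowers the detectable ORs below 1.78 and 1.82. The documents do not support that. The first step uses the same level, so for a single real effect the detectable OR is unchanged. A lower figure would hold only if all effects in the family were real.

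**Conclusion.** The point holds as a minor efficiency improvement. As printed, within-aim multiplicity is handled by single-step Bonferroni, and the article names no step-down procedure. Holm gives the same family-wise control under any dependence. It adds about 3 to 5 points of power per test, and about 6 to 15 points for detecting all effects, when every effect in the family is real at the Table 2 OR and correlations lie between 0 and 0.6. It adds essentially nothing when only one effect is real. N=585 and the ORs of 1.78 and 1.82 remain correct worst-case planning figures and should not be restated. The point does not bear on the decision to leave the two primary outcomes, or the separate aims, unadjusted for one another.

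**What to change.** Before any results are seen, state in both Table 2 footnotes and in the Quantitative data section that, within each aim and outcome, the two or three p values are tested by Holm's step-down procedure at a family-wise two-sided 0.05. Give the first step as 0.05/2 or exactly 0.05/3, not the rounded-up 0.017. Label 0.025 and 0.017 as planning levels for the sample size only.

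The cost is a few sentences. It needs no new data, participants or sample size calculation, loses no planned interval, and weakens no error control. If the full analysis plan already specifies Holm, the footnotes need only the planning-level label and a pointer to it.

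### Table 2's exploratory row on high-risk delivery as an effect modifier repeats the main-effect OR of 1.70 at 90% power, which an interaction with a yes/no modifier does not have

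*Protocol article*

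**What the plan says.** The section on study aims and adequacy of sample size for the quantitative projects describes one calculation and exempts no row of Table 2 from it. It states "Our predictors are continuous variables" and contrasts women at the predictor's mean with women 1 SD above it. The inputs are "Assuming that the frequency of MVD≥0 is 15% in the low-risk group" and an R² "of the predictor regressed on other predictors is 0.5". On that basis 585 women at 1 year are said to give "90% power to detect the minimal OR shown in table 2 for women whose predictor value is 1SD higher".

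Two rows of Table 2 concern effect modification:

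- The exploratory row asks whether a high-risk delivery variable "modifies the association between MVPA in the early postpartum period on pelvic floor support and symptoms at 1 year (exploratory aim"). It prints a significance level of 0.05 and a minimal detectable OR of 1.70, the same pair as the row for the MVPA main effect. The footnote to Table 1 defines the modifier by four delivery events: long second stage, forceps, anal sphincter tear or shoulder dystocia.
- The fitness-by-IAP row prints 0.017 and 1.82. Its footnote says the level was chosen "to accommodate three separate binomial regression models for statistical interaction terms between each test of muscular fitness and IAP".

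No interaction effect size, modifier prevalence or separate interaction calculation is given.

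**The concern.** A main-effect OR per SD and a ratio of ORs between two delivery groups are different quantities with different precision. The coefficient of a continuous-by-binary product term is estimated with information proportional to π(1−π), where π is the prevalence of the modifier. That factor is at most 0.25. A figure calculated for one continuous predictor therefore cannot be carried over to this row unchanged.

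At stake is how a null interaction is read. Set against a printed 90% power at 1.70, it could be taken as evidence that a high-risk delivery does not alter the MVPA association, when the design had a substantial chance of missing a difference of that size.

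**Working it through.** **Inputs from the article:** N = 585; event rate p = 0.15; R² = 0.5; power 90%; two-sided α of 0.05, 0.025 and 0.017. **Assumed, because the article gives no figure:** modifier prevalence π from 10% to 50%, and symptom rates of 30% and 50%.

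**Step 1: reproduce the plan's figures.** For logistic regression on one continuous predictor,

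minimal OR = exp{[z(1−α/2) + z(0.90)] / √[N p(1−p)(1−R²)]}.

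The denominator is √(585 × 0.15 × 0.85 × 0.5) = √37.29 = 6.107.

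- α 0.05: exp(3.242 / 6.107) = 1.70
- α 0.025: exp(3.523 / 6.107) = 1.78
- α 0.017: exp(3.668 / 6.107) = 1.82

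Every OR in Table 2 is reproduced, and only α differs between rows. No interaction-specific input was used.

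**Step 2: the MVPA by high-risk-delivery interaction, support outcome.** With MVPA in SD units and a binary modifier,

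Var(b₃) = 1 / [N p(1−p) π(1−π)(1−R²)] and power = Φ(ln 1.70 / √Var(b₃) − 1.960).

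Example at π = 0.5, R² = 0: information = 585 × 0.15 × 0.85 × 0.25 = 18.65, with square root 4.318. Then 4.318 × 0.5306 − 1.960 = 0.331, and Φ(0.331) = 0.63.

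| Assumed prevalence | 10% | 20% | 30% | 40% | 50% |
|---|---|---|---|---|---|
| Power at ratio 1.70, R² = 0 | 28% | 45% | 56% | 61% | 63% |
| Power at ratio 1.70, R² = 0.5 | 16% | 25% | 32% | 35% | 37% |
| Ratio detectable at 90%, R² = 0 | 3.49 | 2.56 | 2.27 | 2.15 | 2.12 |
| Ratio detectable at 90%, R² = 0.5 | 5.87 | 3.77 | 3.18 | 2.95 | 2.89 |

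The function π(1−π) peaks at 50%, so a prevalence above 50% cannot do better.

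**Step 3: simulation check** (n = 585, 1500 runs per scenario, prevalence 20–50%). Power was 42–61% with no main effects. With assumed main effects (MVPA OR 1.3, delivery OR 2), which raise the event rate, it was 51–67%. With those main effects and R² = 0.5 between MVPA and a covariate entered only as a main effect, it was 49–65%. The R² = 0.5 rows above are thus what follows if the plan's inflation applies to the product term itself; the R² = 0 rows are nearer to a model adjusted only for main effects.

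**Step 4: symptom outcome.** By the same formula at a ratio of 1.70, 30% events and 30% prevalence give 77% (R² = 0) or 48% (R² = 0.5). The most favourable case considered, 50% events, 50% prevalence and R² = 0, gives √(585 × 0.25 × 0.25) × 0.5306 − 1.960 = 1.249, a power of 89%.

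**Step 5: the fitness-by-IAP row.** Both variables are continuous. The product of two independent standardised variables has variance about 1, so the formula in step 1 roughly applies to a ratio of ORs per SD × SD. At 1.82 and α 0.017 it gives 89.8% power with R² = 0.5; simulation without inflation gave about 99%.

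**The case against.** - **The test is inferred.** Only the fitness row has a footnote naming interaction terms. The exploratory hypotheses describe prevalence rising with MVPA, with a high-risk delivery, and further with both, which main effects alone could produce. This is fair, but the stated aim is whether the association is modified. If 1.70 is only the MVPA main effect, the cell does not address its own aim.
- **1.70 could be per SD of the product term.** On that scale 90% power can be met. It then corresponds to a ratio of ORs of exp(0.5306/√π), from 2.12 at 50% prevalence to 3.28 at 20%. The article defines its OR per SD of a predictor and does not mention this scale.
- **The row also covers symptoms, which are more frequent.** This stands and narrows the shortfall. The 28–63% range is for support only.
- **The aim is exploratory.** The data analysis section considers effect modification only where cell sizes permit and promises 95% CIs, so imprecision will be visible. This stands as a reason for lower severity, but does not make the printed figure right.

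A reader might also infer that the fitness-by-IAP row is underpowered, for instance because dividing women at the median of fitness would give a much weaker test. The article proposes no such split, and step 5 shows no shortfall for the continuous test it describes.

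**Conclusion.** The point holds for one row. The 1.70 at 90% power for effect modification by a high-risk delivery is a main-effect figure. For support at the plan's 15% event rate, formula power at a ratio of 1.70 is at most 63% (R² 0) or 37% (R² 0.5) at any prevalence. With R² 0, 90% power would need about 1171 women at 50% prevalence and 3253 at 10%, against 585. The exact size of the shortfall depends on a prevalence the article does not state, and for symptoms on an event rate it does not state.

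It would go too far to conclude that the sample size or the main-effect aims are affected: those figures reproduce. In the fitness-by-IAP row, 1.82 and its power statement stand approximately, and only the label is incomplete. Severity is minor to moderate.

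**What to change.** 1. In the exploratory row of Table 2, delete 1.70, or replace it with a minimal detectable ratio of ORs per SD of MVPA, stating the assumed prevalence of a high-risk delivery and the R². For support this is about 2.1–2.6 at 20–50% prevalence with R² 0, or 2.9–3.8 with R² 0.5.
2. Exempt that row from the 90% power sentence in the sample-size text.
3. In the fitness-by-IAP row, keep 1.82 and its power statement, and label it as a ratio of ORs per SD × SD.

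The cost is two table cells and one sentence, with a less favourable figure in the exploratory row. No participant, test or primary analysis changes.

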### Study aims and adequacy of sample size for the qualitative project

The aims for the qualitative project are given in box 1.

Box 1Study aims for the qualitative projectTo describe primiparous Mexican-American and Euro-American women's experiences and cultural knowledge of postpartum pelvic floor support changes.
To characterise the ways women perceive and make sense of early changes in pelvic floor support as well as the ways they use language and discourse to construct meaning about those changes in the year after their first delivery.To describe how primipara share experiences and cultural understandings of postpartum pelvic floor support with mothers, partners, sisters and confidantes in their families and social networks.To explore the interplay of women's understandings of early changes in pelvic floor support with sociocultural prescriptions/proscriptions regarding physical activity and any resulting postpartum alterations of activity which they may undertake.To collaboratively develop the toolkit of culturally appropriate resources for women, their families and clinicians; to evaluate it for applicability; and to deploy it on a nationally accessible website.

The planned sample of 30 Euro-American and 30 Mexican-American new mothers is expected to achieve conceptual saturation of the data based on prior ethnographic studies;^93^
^94^ that is, we expect that no new relevant themes will be identified from successive interviews, no new relevant categories for a subsequent interviewee will be suggested by the data, and ongoing member checks will validate the developing findings.

